**Methods:**

This is a prospective, single-center, non-randomized controlled trial. A total of 275 patients who meet the inclusion criteria will be enrolled and allocated with a 4:11 ratio of CL to SL, which is based on results of our previous study. All patients will receive same perioperative management and postoperative medications. All EVAR procedures will be performed under standard protocol, utilizing Endurant II or IIs Stent Graft. The configuration of the graft stent will be decided by surgeons and confirmed by final angiography. The primary outcome is 3-year freedom from major adverse limb-graft events (MALEs). Endpoints will be assessed at the following time points: 1, 6, 12, 24, and 36 months.

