**FIGURE 1 F1:**
[figure not shown]
The procedure of screening, randomization and follow-up in the DANCER trial.

**TABLE 1 T1:** Inclusion and exclusion criteria for participants.

Inclusion	Exclusion
Patients are considered eligible if they meet all of the following criteria: 1. Men or non-pregnant women aged ≥ 18 years and with sufficient life expectancy to complete all the processes of the study. 2. Diagnosed with infrarenal abdominal aortic aneurysm (according to ICD I71.3 and I71.4) and indicated for surgical intervention. 3. Local anatomy of bilateral femoral and iliac arteries allows for guide wire passing. 4. Provide written informed consent and agree to participate in the study. 5. Placement of iliac endografts is required during the procedure.	Patients shall be excluded from the trial if they meet any of the following criteria: 1. Unable to tolerate contrast agents, antiplatelets or anticoagulants. 2. Recorded with previous primary repair for AAA, no matter EVAR or open surgical repair.

AAA, abdominal aortic aneurysm; EVAR, endovascular aneurysm repair.

We will recruit patients by putting up posters and advertising online to meet the expected enrollment. In addition, we provide fast-track follow-up for patients who are willing to participate in our study. Figure 2 shows the schedule of enrollment, interventions and assessments, following the template provided by SPIRIT (24).

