### Allocations of intervention

Based on the anatomic features of the aneurysm by intraoperative imaging, surgeons will determine whether to adopt CL or SL configuration. When both configurations are feasible, surgeons will assign the limb configuration based on covariate adaptive matching between the two groups. The major matched covariates are as follows: age, gender and aneurysm diameter. Both surgeons and participants are not blinded to the interventions, and only statisticians who analyze the data are blinded.

The CL and SL configurations are defined as crossed or uncrossed limb grafts in anteroposterior view of the final angiogram, respectively. CL is further subdivided into anterior-posterior (AP) cross and left-right (LR) cross, which correspond to ≥ 50 and < 50% overlapped areas between two limb grafts in the angiogram. SL is similarly subdivided into AP parallel and LR parallel with the same definition.

The included patients will receive the same perioperative management, including blood pressure control, analgesia and medication with antiplatelets and statins. In interventional operating room, both common femoral arteries will be used for percutaneous or cut down access. After administration of 0.5 mg/kg unfractionated heparin, graft stents are placed in accordance with instruction for use by an experienced surgeon of vascular surgery. Treatment procedures are performed under a standard protocol. The Endurant II or IIs Stent Graft (Medtronic, Minneapolis, Minn) is used for repair.

Postoperative medications include antiplatelet monotherapy (aspirin 100 mg once a day or clopidogrel 75 mg once a day) and statins. Patients are expected to take these medications all life unless severe adverse event occurs. Anticoagulants, such as low molecular weight heparin or direct oral anticoagulants, will be used according to surgeons’ decision.

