**Other outcomes**	
**Intraoperative technical outcome**	
technical success rate	Freedom from surgical conversion or mortality, type I or III endoleaks, or graft limb obstruction after the deployment of devices

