### Sample size calculation

We calculate the sample size for this study based on the results of our previous study (22), in which 11.5 and 7.9% of patients suffered from adverse limb events in CL and SL groups, respectively. In this trial, we hypothesize that the freedom from adverse limb events in the CL group is not inferior to that in the SL group. The predetermined non-inferiority margin on the risk difference scale (δ) is set to 0.15 between the two groups. The type I and II error rates are set to 0.05 and 0.2, respectively. As the intraoperative choice of limb configuration is difficult to randomize, the ratio of enrolled patients between the CL and SL groups is set to 4:11 based on our previous cohort study (22). After accounting for a 20% rate of dropout, it is calculated that 73 subjects are needed for the CL group, and this value is 202 in the SL group. All calculations are performed by PASS 15 software.

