### Statistical analysis

Categorical data is expressed as number and rate, while continuous data is expressed as means ± standard deviation if they are normally distributed or median with interquartile range otherwise. Student’s *t*-test or Mann-Whitney *U*-test is used for univariate analysis of continuous data. χ^2^-test or Fisher’s exact test is used for categorical data. For primary analyses, multivariate logistic regression is used to calculate adjusted odds ratio and 95% confidence interval for short-term outcomes. Cox proportional hazard regression analysis and marginal structural model are adopted to assess the association between limb configuration and time-to-event outcomes.

The propensity score to undergo CL or SL is estimated by logistic regression model based on demographic and anatomic information. Inverse probability of treatment weighting adjusted analyses are performed to achieve weighted balance with standardized differences < 0.10. Sensitivity analysis is conducted to stabilize the weights by truncating the non-overlapping tails of the propensity score distributions which below or above the 1st and 99th percentiles. Subgroup analysis is conducted in terms of large aneurysm sac, severely angulated neck, tortuous iliac arteries and iliac landing zone (whether using bell-bottom iliac stent graft). In addition, this analysis will be carried out in AP and LR subgroups. R studio Version 1.2.1335^1^ and Empower (X&Y solutions, Inc., Boston, MA)^2^ are utilized for statistical analysis.

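### Groups are defined only by the final angiogram, so a switched attempt's procedural burden falls on the other group and patients without that angiogram have no group

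*Protocol article*

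**What the plan says.** The Allocations of intervention section describes a decision and then a definition.

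- **Decision.** After intraoperative imaging, "surgeons will determine whether to adopt CL or SL configuration". Where either would be feasible, "surgeons will assign the limb configuration based on covariate adaptive matching between the two groups", with age, gender and aneurysm diameter as the main covariates.
- **Definition.** The next paragraph gives the only operational meaning of the two groups: "The CL and SL configurations are defined as crossed or uncrossed limb grafts in anteroposterior view of the final angiogram, respectively".

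The Abstract (Methods) links the two in one line: "The configuration of the graft stent will be decided by surgeons and confirmed by final angiography". Nothing says which label governs when decision and final image differ.

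Table 2 defines technical success, an intraoperative outcome compared between groups, as "Freedom from surgical conversion or mortality, type I or III endoleaks, or graft limb obstruction after the deployment of devices". The adjustment in Statistical analysis rests on baseline data: "The propensity score to undergo CL or SL is estimated by logistic regression model based on demographic and anatomic information".

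**The concern.** The final angiogram comes after the events that several outcomes measure. By the article's own account, crossing the limbs helps with gate cannulation (Abstract, Introduction), and cannulating the contralateral gate is a difficult step in hostile anatomy (Discussion). Crossing may therefore be a response to trouble met during the case as well as a plan made beforehand.

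Two consequences follow if the definition is applied as written.

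- A standard-limb (SL) attempt that ends crossed is analysed as crossed limb (CL), bringing with it the operation time, radiation, contrast and 30-day events of the failed attempt. A CL attempt that ends uncrossed does the reverse.
- A patient converted to open repair, or who dies, before the final angiogram has no crossed or uncrossed limbs on that image and so belongs to neither group. Such patients are failures under the technical-success definition, and an intraoperative death is also a 30-day death, yet neither would be counted in any group.

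Weighting would not repair this. Difficulty met during the procedure is not among the demographic and anatomic inputs to the propensity score. The covariate-adaptive assignment, the most controlled part of the allocation, is also lost for every switched patient.

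**Working it through.** **The plan's own figure.** Group sizes come from Sample size calculation: 73 CL and 202 SL. They reproduce with CL risk 11.5%, SL risk 7.9%, margin 0.15, one-sided 5% error, 80% power and ratio 4:11:

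n(CL) = [0.115 × 0.885 + (4/11) × 0.079 × 0.921] × (1.645 + 0.842)² / (0.15 − 0.036)² = 61.0, and n(SL) = 61.0 × 11/4 = 167.8, taken as 168.

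Multiplying by 1.2 gives 73.2 and 201.6, that is 73 + 202 = 275. The point concerns a definition and changes none of these figures; they serve only as denominators below.

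**What is assumed.** The documents give no rate of switching, conversion or intraoperative death. The rates, the 60 minutes and the risks in switched patients below are assumptions that show the mechanism, not estimates.

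**Operation time.** Assume both configurations truly take the same mean time, all 73 planned CL cases finish crossed, and a share of planned SL cases finish crossed and take 60 minutes longer.

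| Planned SL finishing crossed | Share of final CL group | CL − SL by final angiogram | CL − SL by planned configuration |
|---|---|---|---|
| 5% (10) | 10/83 = 12.0% | +60 × 10/83 = +7.2 min | −60 × 10/202 = −3.0 min |
| 10% (20) | 20/93 = 21.5% | +12.9 min | −5.9 min |
| 15% (30) | 30/103 = 29.1% | +17.5 min | −8.9 min |

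The two groupings give opposite signs from the same patients.

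**Technical success.** Assume 2 of 73 planned CL cases convert or die before the final angiogram and k others fail through endoleak or limb obstruction. Success is (71 − k)/73 by planned configuration and (71 − k)/71 by final angiogram.

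- k = 0: 71/73 = 97.3% against 71/71 = 100%, a gap of 2.7 points.
- k = 5: 66/73 = 90.4% against 66/71 = 93.0%, a gap of 2.5 points.

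Other types of failure lower both rates but barely narrow the gap.

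**Primary outcome.** Assume unswitched patients have the planning risks ("in which 11.5 and 7.9% of patients suffered from adverse limb events in CL and SL groups, respectively") and a share s of one planned group switches, with event risk r in those patients.

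- *CL to SL only.* By plan: (1 − s) × 11.5% + s × r − 7.9%. By final angiogram: 11.5% − (202 × 7.9% + 73s × r)/(202 + 73s). With s = 10%, r = 20%: 12.35 − 7.9 = 4.5 points against 11.5 − 8.3 = 3.2 points. With r = 40%: 6.5 against 2.5 points. Over s = 5% to 15% and r = 20% to 40%, the difference is 4.0 to 7.9 points by plan and 3.4 to 2.0 points by final angiogram.
- *SL to CL only.* By plan: 11.5% − [(1 − s) × 7.9% + s × r]. By final angiogram: (73 × 11.5% + 202s × r)/(73 + 202s) − 7.9%. With s = 5%, r = 20%: 11.5 − 8.5 = 3.0 points against 12.5 − 7.9 = 4.6 points. With s = 15%, r = 40%: 11.5 − 12.7 = −1.2 points against 19.9 − 7.9 = 12.0 points.

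The first pattern makes the final-angiogram grouping kinder to CL and the second makes it harsher. Direction cannot be known without the switch counts.

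**The case against.** **No reclassification rule is written.** The definition may only explain what crossed means on imaging, and the Abstract treats the angiogram as confirming a decision already made. The choice of analysis set can also sit in an analysis plan that is not shown. It is true that the text is silent on discordant cases. But the final angiogram is the only group definition the article gives, and it is unsuited to outcomes that occur before that image.

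**Final configuration suits the primary outcome.** Type IB or III endoleak and limb occlusion over 3 years concern the graft as implanted. There is no randomization to preserve, and mixing crossed and uncrossed grafts within groups can pull the groups together, which is no safeguard in a non-inferiority comparison. This stands. A reader might infer that the primary comparison is invalid, or that non-inferiority must be shown under both groupings. The documents do not support the first, and the second is a debatable design preference.

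**The most exposed outcomes rank low.** Operation time, radiation, contrast, technical success and 30-day events are all listed under other outcomes. This stands and limits the weight of the point.

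**Few patients lack a group.** Deaths after the final angiogram, including later 30-day deaths, can be classified. Technical success also counts type I or III endoleak and limb obstruction, where grafts are in place. If the closing qualifier on device deployment in that definition covers conversion and death too, the unplaced cases are only those between deployment and the final image. Inclusion criterion 5 in Table 1, "Placement of iliac endografts is required during the procedure", might put patients converted before limb placement outside the study altogether. That narrows the gap but does not close it: those failures would then leave the denominator through eligibility instead.

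**Conclusion.** The point holds in a limited form. The groups are fixed by a result of the procedure although a choice or assignment precedes it. For intraoperative and 30-day outcomes, any switch moves the burden of the attempt to the other group. A patient with no final angiogram is in neither group, although conversion and mortality count as technical failures.

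A reader might infer that these outcomes are necessarily biased, or biased in favour of CL. The documents do not support that: bias requires switching or conversion, no rate is given, and the illustrations run in both directions. They show only that small numbers matter with 73 CL patients: 10 switched SL cases would make up 12% of the final CL group, and 2 unplaced patients would move technical success by up to 2.7 points. For the 3-year primary outcome the final configuration is a defensible exposure. What is needed there is a way to see whether the result depends on that choice.

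**What to change.** - Add one time-stamped case-report field for the configuration chosen or assigned after intraoperative imaging and before limb deployment.
- Use that field as the group for operation time, radiation, contrast, technical success and all 30-day outcomes. Keep conversions and intraoperative deaths in that group as technical failures, and say how inclusion criterion 5 applies to them.
- Keep the final-angiogram grouping for the 3-year limb-graft primary outcome. Report the primary comparison by chosen or assigned configuration as a sensitivity analysis, with the number of switches in each direction.

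The cost is one extra field and one extra analysis, which may disagree with the main one and would then have to be explained. The sample size is unchanged. The article gives 1 December 2021 as the start of recruitment, so for patients already treated the intended configuration may not be reliably recoverable; the number with this field missing should be reported by final configuration, with those who had no final angiogram listed separately.

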### Follow-up

After the procedure, all included patients will receive follow-up in outpatient clinics at 1, 6, and 12 months and annually thereafter. The required routine examinations include history taking, physical examination, blood biochemical index and duplex ultrasound. All biological specimens will be processed in routine procedure and not be used in ancillary or other studies. The computed tomography angiography will be performed to search for detailed information if any adverse event, especially endoleak or limb thrombosis, is found by duplex ultrasound. Patients who are unable to return to the outpatient clinic will be suggested to undergo duplex ultrasonography or computed tomography in local medical institutions, which will send medical records and images back to researchers. For patients who fail to finish the expected follow-up, telephone interview or WeChat message will be used instead to record survival status and postoperative adverse events. Due to no additional harm induced by the trial, all adverse events will be processed according to normal treatment procedure and patients will not automatically quit the group or receive additional compensation.

Patients are defined as dropout if the following events occur: (1) Fail to complete the expected follow-up and could not obtain image or medical records: a subject is considered lost to follow-up if they could not be contacted *via* five attempts by telephone or WeChat message. (2) Make withdrawal consent: all participants have the right to withdraw from the study at any time for any reason without obstruction.

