For efficacy of the CL in practice, however, related studies have drawn inconsistent conclusions, which makes the true effect of CL doubtful. By analysis of computed fluid dynamics, CL showed a tendency to prevent stent thrombosis, accompanied by tolerance for higher wall shear stress and helicity characteristics (16, 17). On the contrary, long-term fatigue and displacement implications were revealed by the same studies and another one demonstrated that it was the angle of the aneurysm neck other than the configuration that affected hemodynamic index (18). Similar controversial outcomes were observed in clinical trials. Two retrospective cohort trials showed that CL group had a longer procedural time and more type II endoleak compared with standard limb (SL) groups; however, technical success rate, postoperative complications, reintervention and overall survival were comparable (19, 20). This result was mirrored in the latest meta-analysis with no significant difference found in perioperative mortality, endoleak or limb occlusion. This study concluded that CL did not confer inferior clinical outcomes compared to SL in the medium term (21).

To further explore this issue, we conducted a cohort study in 2021, which suggested that no significant evidence was found to favor either configuration in terms of adverse limb events, endoleak, reintervention or overall survival (22). A trend toward a lower risk of type IB endoleak was observed in the CL group after stratification by large aneurysm sac or tortuous iliac artery. On the other hand, CL incurred a higher risk of reintervention and adverse limb events in patients with angulated aneurysmal neck. As commented by editors, our previous study showed interesting results and had the advantage of significant enrolled patients and sufficient time of follow up. However, it was subject to its retrospective, observational nature and other limitations. To elucidate this problem, a prospective study with a uniform reporting standard and careful design is required accordingly (23). Therefore, the utility of CL configuration requires further investigation, which propels us to launch this study.

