### Hypothesis to be tested

In AAA patients who receive EVAR, CL is not inferior to SL configuration in terms of safety and efficacy in the short and long term.

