### Outcomes of interest

The primary outcome is 3-year freedom from MALEs, which involves type IB/III endoleak and limb occlusion. Type IB endoleak is defined as persistent direct flow in the aneurysm sac due to inadequate distal seal of the stent graft. Type III endoleak is defined as persistent direct flow resulting from stent graft component separation or fabric tear. Limb occlusion is defined as a total occlusion occurring in limb grafts, regardless of symptoms, or an invasively treated stenosis resulting from thrombus formation (> 50% lumen reduction).

The secondary outcomes involve 3-year freedom from type IA endoleak and 3-year freedom from aortic reintervention. Type IA endoleak is defined as persistent direct flow in the aneurysm sac due to inadequate proximal seal of the stent graft. Aortic reintervention refers to any secondary surgical procedure related to the index EVAR.

Other outcomes consist of three aspects: intraoperative technical outcomes (operation time, radiation exposure time, dosage of contrast medium and technical success rate); short-term postoperative outcomes (length of stay in intensive care unit or vascular ward, acute kidney injury, 30-day overall morbidity, 30-day major adverse cardiac events, 30-day all-cause mortality); long-term outcomes (renal function decline, occurrence of type I/II/III endoleak or stent migration, freedom from major adverse cardiac events, aneurysm related death, overall survival).

Detailed information for outcomes is listed in Table 2.

**TABLE 2 T2:** Detailed information for outcomes.

Outcomes	Definition

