**Long-term outcomes**	
Renal function decline	Diagnosed with chronic renal failure and could not be attributed to other known causes
Type I endoleak	Endoleak due to inadequate proximal or distal seal of the stent graft
Type II endoleak	Endoleak originating from collateral vessels
Type III endoleak	Endoleak resulting from stent graft component separation or fabric tear
Stent migration	Migration from original position for more than 5 mm
Aneurysm related death	All deaths from secondary aneurysm rupture after repair, death within 30 days of any reintervention attributable to the aneurysm or death from other aneurysm-related causes (including graft infection or fistula)

MALEs, major adverse limb-graft events; EVAR, endovascular aneurysm repair; MACEs, major adverse cardiac events.

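### Stent migration over 5 mm is an outcome, but the stated follow-up measures it mainly in patients sent to CT by a duplex finding, so it supports no comparative conclusion

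*Protocol article*

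**What the plan says.** **Outcome.** In the Protocol article, Outcomes of interest, the long-term items under the Other outcomes tier include "occurrence of type I/II/III endoleak or stent migration". Table 2 defines the migration event as "Migration from original position for more than 5 mm". Migration is neither a primary nor a secondary outcome.

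**Imaging.** The Follow-up section states: "The required routine examinations include history taking, physical examination, blood biochemical index and duplex ultrasound". CT angiography is "performed to search for detailed information if any adverse event, especially endoleak or limb thrombosis, is found by duplex ultrasound". Two other routes are given. Patients who cannot come back "will be suggested to undergo duplex ultrasonography or computed tomography in local medical institutions". For those who do not complete the expected follow-up, "telephone interview or WeChat message will be used instead to record survival status and postoperative adverse events".

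**Why migration is of interest.** The Introduction, reporting computational studies of CL, says that "long-term fatigue and displacement implications were revealed by the same studies". The Hypothesis section states that "CL is not inferior to SL configuration in terms of safety and efficacy in the short and long term".

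**The concern.** A shift of a few millimetres has to be measured against a reference position. The text schedules no such measurement for every patient. CT follows a duplex finding, so a graft that has moved without a duplex-visible event has no planned route to being recorded as migrated.

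Two things follow. The recorded migration rate will tend to be too low in both groups. The comparison between groups will also partly reflect who was scanned. The Introduction raises displacement as a possible drawback of CL, and the hypothesis claims long-term safety without limit. A low or similar recorded rate could therefore be taken as reassurance that the follow-up was not able to give, and a higher rate in one group could be an artefact of more scanning.

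**Working it through.** The plan gives no figure for migration, so there is none to reproduce. The sample size (73 CL, 202 SL) and the 0.15 margin concern adverse limb events only. The check sets the passages side by side and then shows the size under stated assumptions.

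**1. Routes to a measurement of graft position after the procedure**

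| Patient | Imaging in the Follow-up text | Position measured by CT? |
|---|---|---|
| Attends clinic, duplex clear | Duplex | No CT planned |
| Attends clinic, duplex shows an adverse event | Duplex, then CT angiography | Yes |
| Cannot return | Local duplex or local CT | Only if CT is the option taken |
| Reached only by telephone or message | None | No |

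The only post-deployment image named for all patients is the final angiogram (Allocations of intervention), where it serves to classify the configuration. The text does not say which image fixes the starting position for migration.

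**2. CT triggers from the protocol's own rates**

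Inputs: adverse limb events in 11.5% of CL and 7.9% of SL patients (Sample size calculation), applied to planned enrolment. This assumes that the rates carry over and that each event is found by duplex.

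- CL: 0.115 × 73 = 8.4, about 8 patients
- SL: 0.079 × 202 = 16.0, about 16 patients
- Total: 24.4 of 275 = 8.9%

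Other findings, such as type IA or type II endoleak, would add triggers. Their number is not given.

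**3. Patients without a triggered CT, for assumed overall trigger shares**

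| Trigger share (assumption) | With triggered CT | Without |
|---|---|---|
| 10% | 28 | 247 |
| 20% | 55 | 220 |
| 30% | 82 | 193 |
| 40% | 110 | 165 |

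Most patients lack a triggered CT for any share below 50%. That is plausible, but the document does not state it.

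**4. Effect on the comparison**

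Let m be the true migration risk and s the fraction of true migrations that are imaged. If patients not scanned were counted as event-free, then:

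observed difference = s_CL × m_CL − s_SL × m_SL

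Illustrations (all values of m and s are assumptions):

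- Equal detection, s = 0.3 in both groups, m_CL = 10%, m_SL = 5%: 3.0% − 1.5% = 1.5 points, against a true 5 points. The difference shrinks toward none.
- CL scanned more, s_CL = 0.4, s_SL = 0.2, m = 5% in both: 2.0% − 1.0% = 1.0 point against CL, where the true difference is zero.
- CL scanned less, s_CL = 0.2, s_SL = 0.4, m_CL = 10%, m_SL = 5%: 2.0% − 2.0% = 0, where the true excess is 5 points.

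The fraction s equals the trigger share only if migration is unrelated to triggers. Migration that causes a duplex-visible endoleak prompts its own CT, which raises s.

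**5. Can the direction be predicted?**

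No. Equal but incomplete detection pulls the difference toward zero. Against that, the planning rates imply limb-event triggers about 11.5 / 7.9 = 1.46 times as often in CL, and the Introduction reports more type II endoleak with CL in two retrospective cohorts. Both would mean more scanning of CL patients and more of their migration found. The text does not show how local CT would divide between the groups.

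**The case against.** The strongest reply is that migration sits in the lowest outcome tier. No formal non-inferiority test rests on it. The events that loss of seal or component separation would produce are captured elsewhere: type IB and III endoleak in the primary outcome, type IA endoleak and reintervention as secondary outcomes. This stands, and it limits the point to one outcome.

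A reader might infer that long-term safety as a whole cannot be concluded. The documents do not support that. Reintervention, aneurysm-related death and overall survival are also followed, and none of them requires a measurement of graft position. For the same reason the hypothesis should not be cut down to duplex-triggered events.

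A reader might also infer that CL carries an established displacement hazard which the trial hides. The Introduction's statement comes from computational work, and the Discussion cites another computational study in which CL changed displacement force only slightly. The question is open. Nor can it be said that the gap favours CL (step 5 of the working).

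A further reply is that denominators and the coding of unassessed patients belong in an analysis plan that is not shown. This stands in part: nowhere does the article say that an unscanned patient counts as free of migration. The mismatch itself, however, lies in what the article states about routine examinations and the CT trigger.

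Finally, Figure 2, the assessment schedule, is not available here, and the sentence on routine examinations is worded as a list of what is included. If the figure schedules CT for everyone, it would need reconciling with the Follow-up text.

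**Conclusion.** The point holds for migration alone. On the Follow-up text, migration without a duplex finding will largely go undetected, and a between-group difference would partly reflect scanning frequency, with an unknown sign. The protocol's own rates account for limb-event triggers in about 24 of 275 patients. Under an assumed total trigger share of 10% to 40%, about 165 to 247 patients have no triggered CT. That share, the migration risks and the detection fractions above are assumptions.

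The text does not allow the statement that CT is done solely after a duplex finding, because local CT for patients who cannot return needs no trigger. That route is optional and itself selective, so it does not repair the comparison.

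**What to change.** In the Follow-up text, Table 2 and the hypothesis, or in the analysis plan:

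- Report migration descriptively by group among patients with post-operative cross-sectional imaging, giving the number imaged as denominator and the reason for imaging (duplex finding, local follow-up, other).
- Treat all other patients as not assessed, not as event-free.
- Name the reference image that defines the starting position.
- State that no comparative conclusion on migration will be drawn, and that the long-term safety statement does not cover it.
- Check Figure 2 against the Follow-up text, and reconcile the two if the figure schedules routine CT.

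The cost is a few sentences and one denominator. It needs no new imaging, no change to patient care and no change to the sample size. The downside is a slightly narrower safety claim.
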